#### ***Immunogenicity:***

- The proportion of patients with binding or neutralizing anti-adalimumab antibodies.
- The proportion of patients with binding or neutralizing anti-adalimumab antibodies and inadequate therapeutic response (achieved PASI 50 or less).

The categorical data will be processed using frequency tables, contingency tables, exact Fisher's test, test for equality of frequencies,  $\chi^2$  test, and Cochran-Mantel-Haenszel test. The categorical data will be described using percentages or proportions.

Correction for multiple comparisons will be performed with the Benjamini-Yekutieli procedure.

Statistical methods will be chosen based on the type and distribution of raw data. Appropriate statistical methods will be determined when all the data are obtained, since data distribution and sample homogeneity cannot be assessed in advance. A list of methods may be expanded if necessary for conducting a high-quality study.

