| Statistical Analysis | 
Methods of analysis
 
Statistical analysis will be performed with the Statistica 10.0 software. The normally distributed data will be analyzed using the dependent-sample t-test and ANOVA. The non-normally distributed data will be analyzed using the Mann-Whitney test and ANOVA. The regression analysis will be applied for quantitative efficacy data. Non-categorical data will be processed using the Fisher's exact test, Yates-corrected <math>\chi^2</math> test and Cochran-Mantel-Haenszel test.
 
Determination of sample size
 
The purpose of the study is to demonstrate that the efficacy of BIOCAD's adalimumab biosimilar (BCD-057) is equivalent to the efficacy of Humira® in patients with psoriasis. The number of subjects was determined with the formula for calculating the sample size in two parallel-group equivalence studies as described in the [Chow Shein-Chung, Shao Jun, Wang Hansheng "Sample Size Calculations in Clinical Research"].
 
Selection of populations for analysis
 
Efficacy analysis
 
To assess whether the study has achieved its objective and to evaluate the treatment efficacy, the analysis will be performed in two populations: the ITT (intent-to-treat) population (all randomized patients) and the PP (per protocol) population (includes subjects who have no major protocol deviations up to and including Week 16). If the patient is withdrawn from the study due to safety-related reasons before the primary endpoint is assessed, he/she will be included in the efficacy analysis and considered a non-responder.
 
Safety analysis
 
The safety population will include all randomized patients (ITT population). In addition, the study report will contain data on serious adverse events reported during screening (if any).
 
Immunogenicity analysis
 
The immunogenicity analysis will include all patients who received at least one dose of BCD-057/Humira®. Patients whose serum samples taken on Day 1 of Week 0 and at least one serum sample taken on any subsequent visit (weeks 16, 33, and 55) are missing/lost/spoiled, will be removed from immunogenicity analysis.
 
PK analysis
 
The PK study will involve a limited population (90 patients from each study arm, 180 subjects total). The PK analysis will include all of these 180 patients who:
 
 
Completed all visits for PK assessment starting from Day 1 of Week 15 to Day 6 of Week 16, except for those who missed more than two PK blood samplings during this period.
 
 |

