### ***4.2. Description of the study type/design, study flow-chart, study procedures and periods***

#### ***Study design***

This clinical study of the efficacy and safety of BCD-057 and Humira® in patients with moderate-to-severe plaque psoriasis is a multicenter, double-blind, randomized, parallel-group study with an active comparator (Phase III).

The study will include 344 patients with definite moderate-to-severe plaque psoriasis diagnosed at least 6 months before signing the informed consent (the diagnosis should be confirmed by source documents). These patients should have the BSA of at least 10%, the PASI score of at least 12, and the sPGA score of at least 3.

Before enrollment, all patients will be given the full information about this clinical study, its purpose and the risks associated with study participation. After signing the informed consent form, the patient will undergo a screening examination (for not more than 4 weeks), which aims at confirming that the patient meets the study eligibility criteria. The Protocol does not provide any additional requirements regarding the diet or physical activity during the screening or study period.

According to the results of the screening exam, the investigator will make a decision whether to include the patient in the study or not. The patients who met the eligibility criteria were centrally randomized (with double blinding) into one of the study arms at a 1:1 ratio. At randomization, all enrolled patients were first stratified by body weight ( $< 80$  kg /  $\geq 81$  kg), prior use of antibodies for the treatment of psoriasis (experienced / naive), PASI score ( $< 20$  /  $\geq 20$ ), and presence of psoriatic arthritis (no / yes). Thus, after stratification, the arms will be balanced by all specified characteristics.

---

 Except for therapeutic monoclonal antibodies or their fragments that are specific for tumor necrosis factor alpha.

- Patients in Arm 1 (n = 172) will receive BCD-057 as SC injections given according to the following regimen: 80 mg on Day 1 of Week 0 followed by 40 mg on Day 1 of weeks 1, 3, 5, 7, 9, 11, 13, 15, 17, 19, 21, and 23.
- Patients in Arm 2 (n = 172) will receive Humira® as SC injections given according to the following regimen: 80 mg on Day 1 of Week 0 followed by 40 mg on Day 1 of weeks 1, 3, 5, 7, 9, 11, 13, 15, 17, 19, 21, and 23.

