#### *Pharmacokinetics:*

- Adalimumab concentration in the serum

The statistical analysis will be performed using two-tailed hypothesis tests. The statistical significance level is 0.05.

The Shapiro-Wilk test will be used to test the qualitative data for normality.

Normally distributed data will be compared using the following tests: the two-tailed Student's *t*-test, Welch's *t*-test, and ANOVA.

Non-normally distributed data will be compared using the following tests: the Mann-Whitney test, Wilcoxon test, Kruskal-Wallis test, and Friedman's test.

To describe the normally distributed quantitative variables, the following parameters will be used: means, SDs, min, max, and coefficient of variation. For non-normally distributed quantitative data, it is planned to use median and quartiles, minimum, maximum, and coefficient of variance.

The statistical hypothesis of the equivalence by the primary endpoint will be tested by comparing limits of the 95% CI with the equivalence margin.

The null hypothesis ( $H_0: |\varepsilon| \geq \delta$ , where  $\delta$  is the equivalence margin) is rejected, and the drugs are considered equivalent if the bounds of the 95% CI for the difference in the mean proportions of PASI 75 responders fall within the equivalence margin ( $\delta = 0.15$ ).

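### Apart from the fixed primary rule, the protocol leaves the choice of test until all data are in, and its synopsis and section 9.1 name conflicting t-tests

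*Protocol*

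**What the plan says.** **Primary.** Section 9.1 declares equivalence if "the bounds of the 95% CI for the difference in the mean proportions of PASI 75 responders fall within the equivalence margin", with a margin of 0.15. The measure, the interval and the margin are all set.

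**All other methods.** The close of section 9.1 states: "Statistical methods will be chosen based on the type and distribution of raw data". It continues: "Appropriate statistical methods will be determined when all the data are obtained, since data distribution and sample homogeneity cannot be assessed in advance". It ends: "A list of methods may be expanded if necessary for conducting a high-quality study".

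**Normality check.** Section 9.1 also states: "The Shapiro-Wilk test will be used to test the qualitative data for normality" (quantitative data are evidently meant). Data that pass go to Student's t, Welch's t or ANOVA. Data that fail go to Mann-Whitney, Wilcoxon, Kruskal-Wallis or Friedman.

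**Synopsis, Methods of analysis.** "The normally distributed data will be analyzed using the dependent-sample" t-test and ANOVA. No independent-sample t-test is named. The synopsis also lists Cochran-Mantel-Haenszel and a regression for quantitative efficacy data, without giving strata or covariates.

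**Stratification.** Section 1.5.1 justifies stratifying by body weight, prior antibody use, PASI score and psoriatic arthritis as factors that can influence the treatment result. Section 4.2 concludes: "Thus, after stratification, the arms will be balanced by all specified characteristics". No section carries these factors, or the baseline value, into a named analysis.

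**Timing.** Section 11.5 opens the blind codes at database lock, before analysis. Section 9.2 reports Week 16 first, then Week 33 and Week 55.

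**The concern.** If the test for an endpoint is settled only when its data are available, the result can influence the choice. Section 9.1 does not require the choice to be made before the codes are opened. If all the data means all 55 weeks, the Week 16 comparison will already have been reported by then. The nominal 5% level of the secondary comparisons is then no longer assured.

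The synopsis and section 9.1 also give different tests for the same normally distributed data. If the synopsis were applied between arms, it would pair patients who have no pairing.

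Finally, the trial stratifies on factors it regards as prognostic and measures every continuous endpoint at baseline. It does not commit to using either, so precision already paid for may be lost.

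**Working it through.** **1. The planned sample size.** The planning response rate and dropout are redacted, so 344 can be matched only under assumptions. For two-sided equivalence with no true difference, n per arm = (z_α + z_β/2)² × 2p(1−p) / δ², with δ = 0.15 and power 80% (z_β/2 = 1.2816).

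- α = 0.05 per side, p = 664/922 = 0.720 (the two 16-week originator studies in Table 14, pooled): (1.645 + 1.2816)² × 0.403 / 0.0225, rounded up, = 154. With 10% dropout, 154/0.9 gives 172 per arm, or 344.
- α = 0.025 per side, p = 86/108 = 0.796: (1.960 + 1.2816)² × 0.3244 / 0.0225, rounded up, = 152. With 10% dropout this gives 169 per arm.

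Several input sets come close to 344, so the figure is not shown to be wrong.

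**2. Effect of choosing the test after the fact.** Null simulation, 172 per arm, 4,000 runs per scenario, nominal level 0.05 (Monte Carlo standard error about 0.0035). The data shapes are assumptions.

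| Data shape | t | Mann-Whitney | Shapiro-Wilk switch | Smallest p of t, Welch, Mann-Whitney |
|---|---|---|---|---|
| Normal | 0.054 | 0.055 | 0.055 | 0.064 |
| Skewed, bounded % change | 0.056 | 0.056 | 0.056 | 0.071 |
| Lognormal | 0.042 | 0.049 | 0.049 | 0.076 |

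The inflation comes from free choice, not from the switch applied as a rule. In the two skewed scenarios the switch and Mann-Whitney columns coincide, as expected if the switch nearly always selects the rank test. For binary data, the smallest p among chi-square, Yates, Fisher and Cochran-Mantel-Haenszel gave 0.053, so there is no material inflation there.

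These rates describe selection towards a significant difference. Selection towards non-significance, which would suit a similarity argument, would instead hide real differences; that was not calculated.

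**3. The t-tests side by side.** The synopsis gives a dependent-sample t-test and ANOVA; section 9.1 gives Student's t, Welch's t and ANOVA. The 172 patients in one arm have no partners in the other, so a paired test has no valid between-arm use. It could serve only for change within an arm.

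**4. Stratifying the primary interval.** With p = 0.72 and 172 per arm, the crude 95% half-width is 1.96 × √(2 × 0.72 × 0.28 / 172) = 1.96 × 0.0484 = 0.0949. If stratum response rates lie d above or below the mean (assumed), R² = d² / (0.72 × 0.28), and the half-width is multiplied by √(1−R²):

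- d = 0.05: R² = 0.012, half-width 0.0943
- d = 0.10: R² = 0.050, half-width 0.0925
- d = 0.15: R² = 0.112, half-width 0.0894

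The reduction is 0.0006 to 0.0055.

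**5. Adjusting continuous endpoints.** If baseline and strata explain a share R² of outcome variance, the standard error is multiplied by √(1−R²). For R² = 0.05, 0.10, 0.20 and 0.30 the factor is 0.975, 0.949, 0.894 and 0.837. This is equivalent to about 181, 191, 215 and 246 patients per arm instead of 172. The protocol gives no R² or baseline correlation, so this is a range and not an estimate.

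**The case against.** The strongest reply is that the only study hypothesis, in section 3, concerns PASI 75 at Week 16, and its rule is set in advance. A reader might infer from the deferral sentence that the primary test is open too. It is not: only the way the interval is computed, and whether it is stratified, remain unstated, and an unadjusted interval here is slightly conservative rather than wrong.

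A reader might also infer that the plan ignores baseline and strata. The documents do not support that. Cochran-Mantel-Haenszel and regression are both listed, and several endpoints are changes from baseline. Naming strata and covariates is commonly left to a statistical analysis plan, which is not shown, so silence on them would not be a finding by itself. The deferral sentence is different: it states a rule, and a plan that fixed the methods beforehand would contradict it.

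On the t-test, the synopsis does not say that its paired test is between arms. A translation slip or a within-arm use is plausible, since the same paragraph sends non-categorical data to Fisher's exact test. The conflict with section 9.1 still needs resolving.

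Distributions could be inspected on blinded, pooled data, which would remove most of the risk. Section 9.1 does not require this. The Benjamini-Yekutieli correction is stated for multiple comparisons; nothing says it covers the choice among tests for one endpoint.

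**Conclusion.** The point holds for the methods other than the primary decision rule. The protocol states a poor rule (methods determined after the data, from an expandable list) and contains a contradiction over the t-test. On continuous endpoints, free choice among three tests would take type I error from 0.05 to about 0.064-0.076 under the simulated shapes. A strictly followed Shapiro-Wilk switch would not inflate it; its drawback is that it can lead to rank tests without a mean difference and CI, which is the more useful summary for supportive evidence of similarity.

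The precision argument is secondary. On the primary, stratification removes about 0.001-0.006 from a half-width of 0.095 under assumed stratum effects. The ANCOVA gain depends on a baseline correlation the protocol does not give. The usual comparison of ANCOVA with a change score assumes absolute change, whereas PASI change is in percent, so no single figure is claimed.

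A reader might go further and say that the trial is already short of power. With 172 per arm, a 95% CI and no true difference, power is 2Φ(0.15/SE − 1.96) − 1. This is 73% at a response of 71.0% and 86% at 79.6%, the two historical 16-week rates in Table 14. With the planning rate and dropout redacted, a shortfall cannot be shown.

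**What to change.** Before any code is opened:

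1. Delete from section 9.1 the sentence deferring the choice of methods, and remove the Shapiro-Wilk gate.
2. Reconcile the synopsis with section 9.1 on the t-test, limiting any paired test to change within an arm. Correct the neighbouring slips (qualitative data tested for normality; non-categorical data sent to Fisher's test).
3. Analyse continuous endpoints by ANCOVA with the baseline value and the four stratification factors. Report the adjusted difference and its 95% CI, with a rank test as sensitivity.
4. Give the primary as a Mantel-Haenszel risk difference stratified by the randomisation factors, with its 95% CI against ±0.15 and the crude difference as sensitivity.

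The cost is protocol wording and programming. No new data, visits or patients are needed.

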## ***9.2. Statistical analysis steps and timelines for reports***

### ***Efficacy analysis using the primary endpoint***

The final report will present analysis of the efficacy and safety endpoints after the 16-week observation of 344 included patients.

### ***Supplementary report No. 1***

First supplementary report will present analytical results for PK, efficacy, safety, and immunogenicity using data obtained after 33 weeks.

### ***Supplementary report No. 2***

Second supplementary report will present analytical results for efficacy, safety, and immunogenicity using data obtained from the entire study (55 weeks).

### ***Supplementary report***

The supplementary report will present analytical results for the secondary efficacy, safety, PK, and immunogenicity endpoints assessed using data obtained over the entire study (55 weeks).

## ***9.3. Planned number of subjects. Justification of sample size, including reasoning or calculations to justify statistical power, and clinical justification of the study***

### ***Efficacy assessment***

The primary endpoint in this study is the efficacy measure, namely the proportion of PASI 75 responders by study arms.

The recent EMA's recommendations (*Guideline on Similar Biological Medicinal Products Containing Biotechnology-Derived Proteins as Active Substance: Non-Clinical and Clinical Issues* [EMA/CHMP/BMWP/42832/2005 Rev1, 2014] and *Guideline on Similar Biological Medicinal Products Containing Monoclonal Antibodies – Non-Clinical and Clinical Issues* [EMA/CHMP/BMWP/403543/2010, 2012]) state that, in general, clinical studies of biosimilars should use an equivalence design. While the study was being planned, the hypothesis of the test product being equivalent to the reference product ( $H_0 : |\varepsilon| \geq \delta$ ,  $H_1 : |\varepsilon| < \delta$ , where  $\varepsilon$  is the true

differences in the mean values of the efficacy endpoint between the arms, and  $\delta$  is the equivalence margin of the test and reference products) was tested using the following error values: type I error is 5% ( $\alpha=0.05$ ), type II error: 20% ( $\beta=0.2$ ); the power of test is 80%.

[REDACTED]

[REDACTED]

[REDACTED]

[REDACTED]

[REDACTED]

[REDACTED]

[REDACTED]

[REDACTED]

[REDACTED]

[REDACTED]

[REDACTED]

[REDACTED]

[REDACTED]

[REDACTED]

[REDACTED]

[REDACTED]

[REDACTED]

[REDACTED]

[REDACTED]

[REDACTED]

[REDACTED]

[REDACTED]

[REDACTED]

[REDACTED]

[REDACTED]

[REDACTED]

[REDACTED]

[REDACTED]

[REDACTED]

[REDACTED]

[REDACTED]

[REDACTED]

[REDACTED]

[REDACTED]

[REDACTED]

[REDACTED]

[REDACTED]

[REDACTED]

[REDACTED]

[REDACTED]

[REDACTED]

[REDACTED]

***9.4. Suitable significance level***

The level of significance is set as 0.05 (5%); the power of the test is set as 0.8 (80%).

***9.5. Statistical criteria for stopping and/or terminating the study***

Not specified by the Protocol.

***9.6. Handling of missing, unevaluable or uncertain data***

All information specified in the eCRF has to be confirmed by appropriate data in the source documents.

After entering all data in the electronic database, an employee keeping the database checks it for inconsistencies, errors, and missing data points. To collect missing data or correct wrong data, the BIOCAD's Data Manager and Medical Expert generate queries, which are patient- and site-specific, i.e. generated for each subject individually. The CRA sends queries to the study site by fax or e-mail. The investigator must respond within 5 working days from the date when the query was received. Copies of responses to queries must be kept at the study site; original responses must be stored at JSC BIOCAD.

When responses to queries are received from investigators, the employee keeping the database checks them for inconsistencies, errors, and missing data points. When all the data from all the sites are collected and entered, the database is locked, and the statistical processing can be performed.

Missing, unevaluable or uncertain data are not subject to replacement.

Uncertain or unevaluable data will be detected during the outlier analysis by examination of Mahalanobis or Cook distance, visual analysis of scattering diagrams and box-plots. Data suspected to be outliers will be processed by the biomedical statistician together with the medical expert and, if necessary, the principal investigator.

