## ***7.2. Methods and timeframes for assessment, documenting, and analysis of efficacy variables***

### ***7.2.1 Timeframes for analysis of efficacy variables***

The analysis of the primary efficacy endpoint will be performed at Week 16 of the blinded therapy with BCD-057/Humira®.

The secondary endpoints (at weeks 24, 33, and 55) will be analyzed when these results are obtained.

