#### ***11.5. Data management and quality control***

In the trials that involve eCRFs, JSC BIOCAD employees (or employees of an authorized CRO) will check the data entered by the study team members for accuracy and completeness. If there are

any inconsistent or missing data points, queries will be generated with a request for clarification. All queries are sent to the study site. A designated member of the study team must immediately answer the request and make all required changes to the database.

At the end of the study, any protocol deviations will be determined. After clarifying protocol deviations and confirming the completeness and accuracy of the data, the database is locked, the blind codes are opened, and the data are ready for analysis.

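### Section 9.6 lets statistical extremeness mark an observed value as unevaluable, with no requirement of proven error or blind review and no rule that source-confirmed values stay in

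*Protocol*

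**What the plan says.** Protocol section 9.6 first describes data cleaning: eCRF entries must be backed by source documents, inconsistencies go to the sites as queries, answers are re-checked, and then "the database is locked, and the statistical processing can be performed". Two further paragraphs follow.

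- The first rules out imputation: "Missing, unevaluable or uncertain data are not subject to replacement".
- The second says how the suspect values are found: "Uncertain or unevaluable data will be detected during the outlier analysis by examination of Mahalanobis or Cook distance", plus visual inspection of scatter diagrams and box-plots. It then assigns the handling of flagged values: "Data suspected to be outliers will be processed by the biomedical statistician together with the medical expert and, if necessary, the principal investigator".

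Other parts of the protocol bear on the same point:

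- **Section 11.5:** at the end of the study, once deviations are clarified and the data are confirmed complete and accurate, "the database is locked, the blind codes are opened, and the data are ready for analysis".
- **Section 7.2.1:** "The analysis of the primary efficacy endpoint will be performed at Week 16 of the blinded therapy".
- **Section 9.8:** the ITT population is all randomized patients, and a PP analysis is run beside it.
- **Synopsis, Statistical Analysis:** for a patient withdrawn for safety reasons before the primary endpoint, "he/she will be included in the efficacy analysis and considered a non-responder".
- **Section 9.7:** the sponsor alone decides on data-modifying allowances and must justify them in the report.
- **Section 9.1:** PASI is listed among the quantitative efficacy data. Equivalence is declared if the 95% CI for the difference in PASI 75 proportions lies within ±0.15.

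**The concern.** An extreme value and a value that cannot be evaluated are different things. Section 9.6 uses the first to detect the second and treats the result like missing data. It sets no threshold, asks for no evidence of error and makes no exemption for PASI. It also does not say that a value which survives a source check is kept.

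This matters for the primary endpoint because PASI 75 is derived from percentage PASI improvement. That scale stops at 100%, and most treated patients lie near the top, so the long tail consists of patients who barely improved or got worse. Those patients are the failures that the endpoint has to count. Setting them aside would condition the analysis on the outcome and would estimate response among patients who did not respond unusually badly. The result would also be uneven: a patient withdrawn for an adverse event is protected as a non-responder, while a patient seen at Week 16 with a very poor response is not.

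**Working it through.** **Inputs from the protocol.** 172 patients per arm; margin 0.15; two-sided 95% CI; Week 16 PASI 75 of 71.0% (578/814) and 79.6% (86/108) in the two 16-week pivotal studies in Table 14.

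**Assumptions, not in the protocol.** Residual PASI fraction follows a beta distribution with first shape 0.5, 0.8 or 1.0, fitted to each PASI 75 rate; a 1.5 IQR box-plot rule is applied to percentage improvement; flagged patients leave the denominator.

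**1. The planned sample size.** n = (1.960 + 1.282)² × 2p(1−p) / 0.15². At p = 0.796 this gives 10.51 × 0.3248 / 0.0225 = 152 per arm, or 169 after division by 0.9 for 10% dropout. At p = 0.75 without dropout it gives 176. So 172 is attainable, but the planning rate and dropout are redacted and the figure cannot be reproduced exactly.

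**2. A fixed example that needs no distribution.** Take 130/172 (reference) and 118/172 (test).

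- All kept: 0.6860 − 0.7558 = −0.0698; SE 0.0482; lower limit −0.0698 − 1.96 × 0.0482 = −0.164. Not equivalent.
- Five test-arm failures set aside (118/167): −0.0492; lower limit −0.144. Equivalent.
- Five reference failures set aside (130/167): −0.0924; lower limit −0.186. Not equivalent.
- Five from each arm: −0.0719; lower limit −0.165. Not equivalent.

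**3. Closed form: a share f of failures dropped in both arms.** p′ = p / (p + (1−f)(1−p)). With 79.6% vs 64.6% and f = 0.3, the rates become 0.796/0.9388 = 0.848 and 0.646/0.8938 = 0.723. The difference shrinks from 15.0 to 12.5 points. The arms are reduced to 161.5 and 153.7 patients, the SE is 0.0458, and equivalence is declared with probability 7.8% instead of 2.5%. At 71% vs 56% the corresponding figure is 5.3%. For f = 0.2 the figures are 5.1% and 3.9%; for f = 0.5 they are 20.3% and 11.4%.

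**4. Simulation with the box-plot rule (6,000 trials per setting; ranges over the three shapes).**

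| True rates, ref vs test | Screening | Removed, ref / test | Mean difference, points | Equivalence declared |
|---|---|---|---|---|
| 71 vs 56 | none | 0 / 0 | 15 | 2.5-2.9% |
| | pooled | 0.9-1.0 / 5.5-5.9 | 13.3-13.6 | 4.8-6.5% |
| | within arm | 4.0-6.3 / 0.4-1.7 | 16.2-17.7 | 2.1-3.0% |
| 79.6 vs 64.6 | none | 0 / 0 | 15 | 2.3-2.5% |
| | pooled | 1.5-2.5 / 7.7-12.5 | 11-12.7 | 8.1-14.5% |
| | within arm | 5.0-8.6 / 3.1-3.6 | 16.2-17.8 | 3.3-3.5% |
| 71 vs 71 | none | 0 / 0 | 0 | 72-74% |
| | within arm | 3.9-6.2 each | 0 | 59-66% |
| 79.6 vs 79.6 | none | 0 / 0 | 0 | 85-86% |
| | within arm | 5.0-8.6 each | 0 | 74-77% |

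The closed-form value without removal is 2.5%; the spread around it in the rows without screening is simulation error. In every setting the rule removed non-responders only and never a responder.

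**The case against.** Three stronger readings are tempting, and the protocol supports none of them as fact.

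- **That outliers are deleted.** The text says they will be processed, and no replacement most naturally means no imputation. The option of involving the principal investigator suggests a check against source. The ITT set is all randomized patients, so dropping an observed patient would depart from section 9.8. Deletion is an inference. It is also not excluded, because nothing says how a Week 16 PASI judged unevaluable is counted.
- **That the review happens after the codes are opened.** Section 9.6 describes it after lock but does not date it. Section 11.5 ties code opening to the end of the study, after accuracy has been confirmed, whereas section 7.2.1 places the primary analysis during blinded therapy. The order for Week 16 cannot be read from the protocol. What is certain is that no passage requires the review to be blind or to precede lock.
- **That the result moves toward equivalence.** Pooled screening, loss of an equal share of failures in both arms, or loss from the worse arm does this. Within-arm screening or loss from the better arm does the opposite, and five failures from each arm left the example unchanged.

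It is also fair to say that PASI 75 is binary while these tools are for quantitative data, that the simulated rule is hypothetical, that thresholds commonly belong in a statistical analysis plan (not available here), and that section 9.7 requires data-modifying decisions to be disclosed. The binary form gives little protection, because the response is derived from a PASI score that section 9.1 treats as quantitative. Disclosure in the report explains a choice afterwards and does not prevent it. The point is also not that a threshold is absent: section 9.6 positively states that outlier statistics detect unevaluable data.

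**Conclusion.** The point stands as a badly fixed rule. Section 9.6 allows an observed, source-confirmed but extreme PASI value to be classed with missing data by case-by-case judgment, and no other section keeps it in the analysis or requires the judgment to be blind.

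If such values were set aside, the removals would be essentially all PASI 75 failures. With a true difference at the margin, pooled screening would raise false equivalence from 2.5% to about 5-14% and shrink the observed difference to about 11-13.6 points. Within-arm screening would widen it to about 16-18 points and, under true equality, cut power from about 86% to 74-77% (at 79.6%) or from about 73% to 59-66% (at 71%). In the count example, five decisions in one arm reverse the conclusion.

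The simulated sizes rest on the assumed beta distributions, response rates, 1.5 IQR rule and removal of flagged patients. The count example and the closed form assume only the rates and the removals. Neither deletion, nor review with treatment known, nor a bias in the sponsor's favour is established by the text.

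**What to change.** Reword the last two paragraphs of section 9.6 so that:

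1. outlier screening serves only to raise data queries and is completed on blinded, pooled data before the data cut or lock for each analysis, including Week 16;
2. every value confirmed against source stays in the primary and other main analyses, and extremeness alone never makes a value unevaluable;
3. any analysis that leaves out extreme values is labelled a sensitivity analysis.

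How to count a PASI value that is proven wrong and cannot be corrected is a separate missing-data question and need not be settled here.

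The cost is a wording change and a screening step scheduled ahead of each lock. No extra data or patients are needed.
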